### Trial conduct and data monitoring

#### Study duration

Enrolment period: 2016–2018

For a given subject: 42-day participation after randomisation

Duration of research: 44 months

End of the research term following participation of the last enrolled person: 1 year

#### Data collection and management

Data will be anomymised in accordance with the law dated 6 January 1978. Data will be collected electronically. Data will be analysed in accordance with the methodology described in MR 06001 form of the French Data Protection Authority by [name] epidemiology and public health biostatistics platform Lille University Hospital Lille. Access to data will be restricted to individuals who are directly involved in the study. Data may be modified by any physician participating in the study or a fellow working with a physician participating in the study. Trial data will be archived for at least 15 years after the trial has ended.

### Study outcomes

#### Primary endpoint

The primary endpoint is the additional blood loss volume measured between inclusion (T0) and 6 h after inclusion (T360).

#### Secondary clinical endpoints

The secondary endpoints will measure the impact of the study product and dose on total blood loss, intensity and rate of postoperative anaemia (decrease of haemoglobin preoperative to day 2, nadir of haemoglobin, number of patients with haemoglobin under 8 g/dL or a 4-point decrease at any time), immediate and late red blood cell transfusion and usage of prohaemostatic products, rate of surgical interventional procedures, such as arterial ligature, or surgical compression of the uterine wall or internal compression balloon, CS duration and general anaesthesia frequency, rate of postoperative organ failure, rate and duration of intensive care hospitalisation, breast-feeding duration, death, and the safety of the dose-ranging use of TA in haemorrhagic CS, and side effects related to the product.

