### Study population

The inclusion criteria for the experimental haemorrhagic group concern each patient experiencing a bleeding volume of more than or equal to 800 mL due to surgery or to uterine atony during an elective or non-emergency CS. This experimental group will receive a low dose or a standard dose of treatment (treatment groups) or placebo (control group). The non-haemorrhagic group, where patients experience a bleeding volume of less than 800 mL, is a reference group for biology and will be sampled to obtain a reference profile for the direct plasmin generation test in CS. All patients receive complete information, give their written consent and are covered by social security.

Non-inclusion criteria are as follows: hypersensitivity to the product or its excipient, previous or ongoing arterial or venous thrombosis, disseminated intravascular coagulopathy, except disseminated intravascular coagulopathy (DIC) associated with a predominant fibrinolytic profile, renal failure, previous seizures, severe HELLP syndrome, emergency CS, administration of TA before inclusion, inherited haemorrhagic diseases and low-molecular-weight-heparin administration within 24 h before inclusion, previous inclusion in an interventional trial for 2 months, or patient being unable to consent.

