##### Methods of storing the investigational drug

The preparation of 10-mL study syringes will be achieved by the pharmacy of the sponsor in numbered boxes depending of the randomisation by centre. Every syringe and kit will be labelled according to the current regulation. The boxes are allocated to the centres via their pharmacy research unit and four boxes will be available on the labour ward in order to respond to elective or emergency inclusion processes. The product is allocated to the patient following an increasing number system. Boxes are returned to the centre pharmacy for tracing.

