#### Blind randomised treatment administration

The preparation of the two dose regimens and the placebo is planned for each centre by the promoter to certify the double-blind character of the trial. The products will be prepared as ready to use

The treatment is presented in a blinded 10-mL syringe containing 0, 0.5 g or 1 g TA, respectively, for each TA0 (placebo), TA½ and TA1 group. The single-dose injection will be independent of patient weight in order to allow a pharmacokinetic analysis of the weight influence. Treatment administration is performed after birth.

The time of injection onset is noted as T0. Intravenous injection will be performed with a strict control of 1-min duration and the end of injection defines T1 = T0 + 1 min, the time of the plasma peak of TA.

Rescue administration of a second dose of 1 g TA is allowed only if haemorrhage becomes severe (more than 1500 mL). If this condition cannot be respected, the patient will be excluded a posteriori. The inclusion number will be kept for the patient presenting with this deviation and the follow-up and visits will continued and analysed in the intention-to-treat analysis.

The investigator can use, at any moment and in any situation that seems necessary, the unblinding procedure by opening the envelopes attached to the treatment.

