##### Data collection

Inclusions are performed 24 h per day, 7 days a week. Each patient admitted for an elective or non-emergency CS during labour will be informed before the CS commences and a signed consent will be obtained. Patients will be included in the haemorrhagic group when haemorrhage exceeds 800 mL. Blind injection of the 10 mL-vial containing 0, 0.5 g or 1 g of TA will be performed over 1 min between T0 and T1 after injection. Transfusion, maternal haemodynamic, resuscitation measure, uterotonic and invasive procedure data and maternal morbidity parameters are recorded before inclusion (T0) and at T30, T60, T120 and T360, respectively 30, 60, 120 and 360 min after inclusion and at day 2 (±12 h) and day 42 (±14 days) postpartum. D42 data collection will be performed using telephone interview.

Various margins of time will be allowed for the timing of the data collection: T1 is the reference time and the time of the TA plasma concentration peak and no time margin will be allowed (sample exactly at the end of the TA injection). The time margins allowed for T30, T60, T120, T360 will be 5, 5, 10 and 60 min respectively. The margins allowed for day 2 will be 12 h and for day 42, 14 days. The real data collection time will be collected exactly anyway to allow the pharmacodynamic analysis.

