#### Statistical analysis

Statistical analyses will be independently performed by the Biostatistics Department of University of Lille under the responsibility of [name]. Data will be analysed using SAS software (SAS Institute Inc, Cary, NC, USA) and all statistical tests will be performed with a two-tailed alpha risk of 0.05. A detailed statistical analysis plan will be written and finalised prior to the database lock. Baseline characteristics will be described for each group. The quantitative variables will be expressed as mean and standard deviation in cases of normal distribution and median and interquartile if not. The normality of distributions will be checked graphically and using the Shapiro-Wilk test. Qualitative variables will be expressed as frequencies and percentages.

For the main objective, the blood loss measured in each experimental group (low-dose and high-dose) will be compared to that of the placebo group by using an analysis of covariance adjusted for baseline blood loss volume and centre effect. In cases of non-normal distribution (except if a log-transformation could be applied to normalise the data), relative blood loss volume will be calculated and compared using a Mann-Whitney *U* test.

Analyses will be done on an intention-to-treat basis especially concerning the patients receiving a rescue dose of TA in cases of severe (>1500 mL) haemorrhage. An exploratory analysis will be performed on all the measures of the primary endpoint (T0, T30, T60, T120 and T360). We will use the linear mixed model in order to compare the evolution of the primary endpoint according to each experimental group and the placebo group. This model allows the performing of an analysis of variance (ANOVA) test for repeated measures taking into account the correlation between the repeated measures. The choice of the covariance model will be based on the AIC criteria. Post hoc analysis at each time of measure will be performed using a Bonferroni correction.

For the secondary objectives, secondary endpoints will be compared between each experimental group and the placebo group by using the chi-square test or Fisher’s exact test for qualitative parameters, and using Student’s *t* test or the Mann-Whitney *U* test for quantitative parameters. For the quantitative parameters measured at each time, we will employ the linear mixed model, as previously described for the main objective. The incidence of adverse events will be analysed in a descriptive way.

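### Caesarean duration, and possibly general-anaesthesia frequency, include a part that precedes T0 and is compared unadjusted: a loss of precision and dilution, not bias

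*Protocol article*

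**What the plan says.** The Secondary clinical endpoints section gives a single list of outcomes meant to show the impact of product and dose. It includes "CS duration and general anaesthesia frequency" and gives neither item a start point or a denominator.

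The timing of entry is set elsewhere in the article:

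- Study population: the qualifying bleed is one "due to surgery or to uterine atony during an elective or non-emergency CS".
- Data collection: "Patients will be included in the haemorrhagic group when haemorrhage exceeds 800 mL".
- Methods of storing the investigational drug: "The product is allocated to the patient following an increasing number system". Allocation therefore takes effect when the next box is used.
- Blind randomised treatment administration: "Treatment administration is performed after birth", and "The time of injection onset is noted as T0".

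Under Statistical analysis, "secondary endpoints will be compared between each experimental group and the placebo group" by chi-square or Fisher tests for qualitative variables and by Student's t or Mann-Whitney tests for quantitative ones. No covariate is named. The primary endpoint is handled differently: it is limited to the interval from T0 to T360, and its analysis of covariance adjusts for baseline blood loss and centre.

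**The concern.** Incision, delivery and the initial anaesthetic come before T0. Whatever the study drug does, it cannot shorten minutes already elapsed or undo an anaesthetic already given. The exclusion criteria listed in the article do not bar women who are under general anaesthesia when they start to bleed.

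The two endpoints are affected differently. For duration, the expected difference in minutes between arms is the same for total and post-T0 time; what may change is the spread around it. For general anaesthesia, women already under it count as events in every arm whatever the treatment, so both the absolute difference and the risk ratio shrink. In either case a null result could be read as no effect on remaining operating time or on conversion to general anaesthesia, when the endpoint was simply a blunt measure of it.

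**Working it through.** **The plan's own figure.** The article gives no power, SD or event rate for these endpoints. Its only clinical sample size is for blood loss: 133 (SD 252) against 58 (SD 96) mL, two-sided 5%, 80% power. Pooled SD = √((252² + 96²)/2) = 190.7, and 2 × (1.96 + 0.84)² × 190.7²/75² rounds up to 102. The t correction (1.96²/4 = 0.96) gives 103, as stated. The point below does not touch that figure.

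**Duration.** Let A be minutes from start of surgery to T0, and B minutes from T0 to end of surgery. Total = A + B.

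- Var(total) = SD_B² + SD_A² + 2ρ·SD_A·SD_B.
- After adjusting for A, the residual variance is SD_B²(1 − ρ²). It is the same for total and post-T0 time, because they differ only by A.
- Break-even, where total is as precise as unadjusted post-T0 time: ρ = −SD_A/(2·SD_B).

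Assumptions, none from the documents: SD_B = 20 min; SD_A = 5, 10 or 20 min; unadjusted post-T0 time (variance 400) has 80% power. Then power = Φ(2.80·√(400/V) − 1.96) for variance V.

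| ρ | Total, SD_A 5 | Total, SD_A 10 | Total, SD_A 20 | Adjusted for A |
|---|---|---|---|---|
| 0.3 | 485 (72%) | 620 (61%) | 1040 (41%) | 364 (84%) |
| 0 | 425 (78%) | 500 (71%) | 800 (51%) | 400 (80%) |
| −0.25 | 375 (82%) | 400 (80%) | 600 (63%) | 375 (82%) |
| −0.5 | 325 (87%) | 300 (90%) | 400 (80%) | 300 (90%) |

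Break-even lies at ρ = −10/40 = −0.25 for SD_A = 10 and −20/40 = −0.5 for SD_A = 20. The adjusted column is never worse than total or than unadjusted post-T0 time. Those two correspond to fixed coefficients for A, while adjustment uses the best one. Its price is one degree of freedom.

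**General anaesthesia.** Let q be the share already under general anaesthesia at T0 and p the conversion risk afterwards. Any general anaesthesia = q + (1 − q)p. Assumptions, again not from the documents: p = 15% against 5%, and q from 0 to 20%. The 114 per arm is the article's recruitment target. Power is Φ[(|d| − 1.96·√(2p̄(1 − p̄)/n)) / √((p₁(1 − p₁) + p₂(1 − p₂))/n)]. For new general anaesthesia, n = 114(1 − q).

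| q | Any GA, control vs treated | Risk ratio | Power, any GA | Power, new GA only |
|---|---|---|---|---|
| 0 | 15.0% vs 5.0% | 0.33 | 71% | 71% |
| 2% | 16.7% vs 6.9% | 0.41 | 63% | 70% |
| 5% | 19.3% vs 9.8% | 0.51 | 53% | 69% |
| 10% | 23.5% vs 14.5% | 0.62 | 41% | 67% |
| 20% | 32.0% vs 24.0% | 0.75 | 27% | 62% |

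For q = 5%: 0.05 + 0.95 × 0.15 = 0.1925 and 0.05 + 0.95 × 0.05 = 0.0975. The difference is 0.095 instead of 0.10, and the ratio is 0.51 instead of 0.33.

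**The case against.** The endpoint list is one sentence in a journal article. It does not define the start of caesarean duration or say which anaesthetics count, and a detailed analysis plan, promised before database lock, may do so. This stands for general anaesthesia: the wording could mean conversion after inclusion, and the dilution arises only if it means any general anaesthesia. It carries less weight for duration, because the duration of a caesarean ordinarily starts before T0 and the article itself names the unadjusted tests.

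The second objection is stronger. A reader might infer that total duration must be the less precise measure, for example that it wastes 20% to 50% of the patients (the first SD range at ρ = 0: variance ratios 500/400 = 1.25 and 800/400 = 2.0). The documents do not support that. T0 is set by when bleeding reaches 800 mL, so a woman included early may have more of the operation left. A negative correlation is plausible, and at −0.5 with a pre-T0 SD of 10 min the unadjusted total is the more precise of the two, at 90% against 80%. Simply replacing total by post-T0 time could therefore lose power. The variance ratio also does not translate directly into patients lost if Mann-Whitney is used.

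Third, the trial is randomised and double-blind, so the pre-T0 part is balanced in expectation. That is correct, and it limits the point to precision and dilution.

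**Conclusion.** The point holds in a limited form. As listed, caesarean duration includes operating time before T0, and general-anaesthesia frequency, if it means any general anaesthesia, includes anaesthetics given before T0. Neither can respond to treatment, and the planned tests do not adjust for them. A reader might infer a biased comparison or an inflated false-positive rate; randomisation rules out both. The primary endpoint and the sample size are unaffected.

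The size cannot be computed from the documents. For duration it runs, under the assumed SDs, from a marked loss (80% to 41% power at ρ = 0.3 with equal SDs) through no loss (ρ of −0.25 or −0.5, according to the pre-T0 SD) to a gain. For general anaesthesia the direction is certain once any woman is already under it at T0. The extent depends on that unknown share: with assumed conversion of 15% against 5%, power is 63% against 70% at a share of 2%, and 27% against 62% at 20%. These are two minor secondary endpoints, so this is a worthwhile refinement and not a flaw in the trial's main conclusion.

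**What to change.** In the analysis plan, before database lock and unblinding:

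1. Analyse operating time with adjustment for the time from start of surgery to T0. On the scale of minutes, total and post-T0 duration then give the same treatment effect. If a log scale is needed they no longer coincide, so name one of them in advance.
2. Define the anaesthesia endpoint as new general anaesthesia after T0 among women not under it at T0. Status at T0 precedes any treatment effect, so this restriction does not disturb the randomised comparison.
3. Keep total duration and any general anaesthesia as unadjusted description.

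The cost is small but not nil. T0 is already recorded. Caesarean start and end times and anaesthetic status at T0 must be taken from the anaesthesia record. The Data collection section does not name type of anaesthesia among the items recorded at T0, and Trial status shows that inclusion has begun, so this retrieval must also cover women already enrolled. No extra patients or visits are needed.

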#### Secondary biological endpoints

The secondary biological endpoints measure the impact of the study product and dose on D-dimers level and haemostasis parameters, specifically focussed on the diagnosis and evolution of fibrinolysis, plasmin generation and plasma and uterine TA concentrations.

### Statistical method

#### Sample size calculation

The sample size computation is based on the expected difference between the placebo group and the low-dose group and available data on the TA use in active PPH.

Ducloy et al. recruited patients who experienced moderate PPH after a vaginal delivery. The treatment was a TA uniform high dose: 4 g over 1 h, then 1 g/h over 6 h. T0–T360 blood loss after inclusion was estimated at 133 ± 252 mL (mean ± standard deviation) in the placebo group and at 58 ± 96 mL in the treated arm. Kolsi et al. recruited patients who experienced moderate PPH during CS and tested a uniform TA dose of 10 mg/kg. The TA group received 10 mg/kg of TA as an induction dose within 12 min after second-line uterotonic drug onset and 1 mg/kg/h as maintenance within the two following hours. The placebo group received the same volumes of normal saline. The average of total bleeding was 1313 ± 1432 mL in the TA group vs 2089 ± 1556 mL in the placebo group (*p* = 0.03). The WOMAN trial recruited patients who experienced bleeding after vaginal delivery or CS [24]. The design of the WOMAN trial used a 1-g single TA dose. There was no volume measurement request in the study design. The recruitment concerns mostly low-resource countries and the criterion was hysterectomy and/or mortality rate. The first results led to more than 4% and 2%, respectively, of the primary criterion, 10 times higher than European morbidity rates that cannot be extrapolated.

Given that there is no available data on the impact of low TA dosage on blood-loss reduction after inclusion, and considering a maximal 50% reduction as previously observed after higher dose administration, the required number of subjects is 103 by group for a type I error of 5% and 80% power. Considering a maximum of 10% of dropouts or missing data, we will recruit 114 haemorrhagic patients by group for a total of 342 patients.

In order to compare the specific fibrinolysis inhibition parameters with the recent thrombin-plasmin potential generation in a well, a subgroup of patients will be sampled for these specific biological tests and a complementary group of non-treated, non-haemorrhagic CS patients will be included in an observational sequence of clinical and biological assessments. The number needed to observe these pharmaco-biological secondary objectives has been calculated regarding the inhibition of fibrinolysis as diagnosed by the number of patients for whom the D-dimer-level increase between 30 and 120 min was negative or null (EXADELI trial [21]). The number necessary to treat for this substudy is 48 patients in each of the three haemorrhagic groups and 48 patients in the reference non-haemorrhagic group, in total 192 patients. These substudy patients will be selected out of the 342 patients of the experimental groups and recruited during the daytime when sampling, collection and freezing are available.

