**Methods/design:**

The current study proposal is a blinded, randomised controlled trial with the primary objective of determining superiority of either 1 g of TXA or 0.5 g of TXA, in comparison to placebo, in terms of 30% blood-loss reduction at 6 h after non-emergency haemorrhagic caesarean delivery (active PPH > 800 mL) and to correlate this clinical effect in a pharmacokinetics model with fibrinolysis inhibition measured by an innovative direct plasmin measurement regarding plasmatic TA concentration.

A sample size of 342 subjects (114 per group) was calculated, based on the expected difference of 30% reduction of blood loss between the placebo group and the low-dose group, out of which 144 patients will be included blindly in the pharmaco-biological substudy. A non-haemorrhagic reference group will include 48 patients in order to give a reference for peak plasmin level.

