Only one randomised controlled study (EXADELI trial) tested TA efficiency in active PPH following vaginal delivery [21]. A high dose of 4 g was administered, followed by a continuous infusion of 1 g/h. The EXADELI trial demonstrated a mild, but significant, reduction of the bleeding volume (173 mL vs 221 mL in the control group) and a significant reduction of the delay for PPH cessation measured as a blood flow of less than 50 mL per 10 min (Fig. 2) [21]. Although limited, the bleeding volume reduction was associated with a reduction of the percentage of patients developing severe morbidity, such as anaemia or haemorrhagic shock [21]. Mild side effects were observed, including nausea and visual disturbances, but no acute kidney injury nor seizure or thromboembolism were observed. Renal function was similar or even better in the TA group. Deep vein thrombosis complicated catheter insertion in two patients in the control group and three in the TA group [21]. The major point of the EXADELI trial was the strict measurement of PPH bleeding on special graduated bags and the strict respect to the French timed PPH management [22]. Concomitant administration of prohaemostatic treatments was avoided, except for untraceable PPH, enabling the observation of the natural course of PPH-induced coagulopathy. TA clinical efficiency to reduce bleeding in the haemorrhagic caesarean context has not been previously published. In the only (unpublished) Tunisian randomised, placebo-controlled trial in haemorrhagic CS, TA administration induced a reduction of blood loss and transfusion need (*p* = 0.03). Because the absence of academic literature on CS and the low level of evidence after vaginal delivery, current 2014 French guidelines for PPH management restricted the use of TA to late administration in massive haemorrhage: ‘Tranexamic acid may be of interest in PPH treatment, even if its clinical interest has not been demonstrated in an obstetrics setting. Every clinician is free to use TA. If used, the expert group suggests the administration of a 1-g dose only if PPH resists prostaglandins’ [22]. The WOMAN trial aimed to assess the impact of the early administration of TA on death and hysterectomy in women experiencing PPH [23, 24]. Between 2010 and 2016, 20,060 women with a clinical diagnosis of PPH in 21 low- and middle-income countries were included in this randomised, double-blind, placebo-controlled trial to intravenously receive either 1 g TA (*n* = 10,051) or placebo (*n* = 10,009) in addition to standard care. The WOMAN trial found that TA decreased death due to bleeding (155 (1.5%) vs 191 (1.9%), RR 0.81; 95% CI 0.65–1.00; *p* = 0.045), especially in women given treatment within 3 h of giving birth (89 (1.2%) vs 127 (1.7%), RR 0.69; 95% CI 0.52–0.91; *p* = 0.008). Laparotomy for bleeding was also reduced (82 (0.8%) vs 127 (1.3%), RR 0.64; 95% CI 0.49–0.85; *p* = 0.002) after CS and vaginal delivery. The original composite primary endpoint was not reduced (534 (5.3%) vs 546 (5.5%), RR 0.97; 95% CI 0.87–1.09; *p* = 0.65). Adverse events were not increased in the TA group vs placebo: thromboembolic events (30 (0.3%) vs 34 (0.3%)), seizures (33 (0.3%) vs 43 (0.4%)), and renal failure (129 (1.3%) vs 120 (1.2%)). One could suggest that the TA benefit on mortality may be higher in women with severe PPH, then aim to reserve TA for the more severe situations. However, the data showed that the delayed administration of TA was associated with potential harm. Thus TA, if used, should be given early and empirically as soon as a PPH is diagnosed, and before severe haemorrhage. As the study was based on robust clinical endpoints, neither blood loss estimation nor haemoglobin drop were available. There was no subgroup analysis of TA efficacy according to the volume of bleeding. Laboratory results were not included in the primary analysis but were assessed in a few centres as a part of a secondary analysis [25]. The biological effect of the high TA dose administered in the EXADELI trial was observed and compared to a non-treated haemorrhagic group and a non-haemorrhagic postpartum group. Significant excessive fibrinolysis was noted in the untreated haemorrhagic group vs the non-haemorrhagic group at PPH onset. This excessive fibrinolysis was inhibited in the TA-treated group 30 min and 2 h after TA administration, as demonstrated by the inhibition of the D-dimers and PAP increases (Fig. 3) [7].

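### One sample size is attributed to a 30% reduction in the abstract and a 50% reduction in the Methods, and neither gives 103 per group on the document's primary-endpoint figures

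*Protocol article*

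**What the plan says.** The abstract (Methods/design) sets the primary objective "in terms of 30% blood-loss reduction at 6 h after non-emergency haemorrhagic caesarean delivery" and says that 342 subjects, 114 per group, were calculated "based on the expected difference of 30% reduction of blood loss between the placebo group and the low-dose group".

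The Sample size calculation section also names placebo versus low dose as the comparison that drives the number, and it concedes that no low-dose data exist. It then derives the number from a different effect: "considering a maximal 50% reduction as previously observed after higher dose administration, the required number of subjects is 103 by group". The error rates are a 5% type I error and 80% power, and the Statistical analysis section adds that "all statistical tests will be performed with a two-tailed alpha risk of 0.05". An allowance of 10% for dropout takes 103 to 114 per group.

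Two sets of means and SDs are quoted as background:
- a high-dose trial after vaginal delivery, with T0–T360 loss of "133 ± 252 mL (mean ± standard deviation) in the placebo group and at 58 ± 96 mL in the treated arm";
- a caesarean trial, with total bleeding of 1313 ± 1432 mL on tranexamic acid and 2089 ± 1556 mL on placebo.

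The section does not say which of these, if either, produced 103. The primary endpoint is additional blood loss from T0 to T360.

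**The concern.** One sample size cannot be the 80%-power answer to both a 30% and a 50% reduction under the same inputs. On a fixed scale and SD, the required number varies with the inverse square of the effect, so moving from 50% to 30% multiplies it by (50/30)² = 2.8.

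The low-dose comparison sizes the trial, and 30% is the effect named in the abstract's objective. If the 0.5 g arm shows no significant difference, readers will take the abstract's sentence as a guide to what the trial could have detected. Without the planning mean, SD and scale they cannot tell whether a 30% effect was within reach.

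**Working it through.** **Inputs.** Two-sided alpha 0.05 (Statistical analysis); power 80%, 1:1 allocation (Sample size calculation). T0–T360 loss: control 133, SD 252; treated 58, SD 96. Total bleeding in the caesarean trial: control 2089, SD 1556; treated SD 1432.

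**Formulas.** n per group = (1.960 + 0.842)² × (s₁² + s₂²) / Δ², where (1.960 + 0.842)² ≈ 7.849. Power ≈ Φ(Δ / √[(s₁² + s₂²)/n] − 1.960). The unequal-variance t test moves n up by one to three.

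**1. Reproducing 103.** Δ = 133 − 58 = 75 mL, and 75/133 = 56%. s₁² + s₂² = 252² + 96² = 72,720. n = 7.849 × 72,720 / 75² = 101.5 by the normal formula and **103** by the unequal-variance t test.

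**2. The two stated effects on the same endpoint.** 50% of 133 is 66.5 mL; 30% is 39.9 mL. With SDs 252/96 and n = 103, the standard error is √(72,720/103) = 26.6 mL. With SD 252 in both arms it is √(127,008/103) = 35.1 mL. Results by t test:

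| Reduction | SDs | n per group for 80% | Power at 103 |
|---|---|---|---|
| 56% (75 mL) | 252/96 | 103 | 80% |
| 50% (66.5 mL) | 252/96 | 131 | 70% |
| 50% | 252/252 | 227 | 47% |
| 30% (39.9 mL) | 252/96 | 361 | 32% |
| 30% | 252/252 | 628 | 20% |

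With all 114 evaluable, power for 30% is 35% or 22%.

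**3. Log scale (assumption: lognormal matched to 133 ± 252).** Log SD = √ln(1 + (252/133)²) = 1.234. A 30% reduction is −ln 0.7 = 0.357. n = 2 × 7.849 × 1.234² / 0.357² ≈ 189, and power at 103 is about 54%. A 50% reduction would need 50 per group, so on this scale the shortfall concerns 30% only.

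**4. Other routes to about 103.**
- 30% of the caesarean trial's total bleeding: Δ = 626.7 mL, SD 1556 in both arms, n = 97 (normal) or 98 (t). Dividing 98 by the Mann-Whitney efficiency 0.955 gives 102.6, so 103. Total bleeding is not the primary endpoint.
- 50% of 133 mL tested one-sided with SDs 252/96 gives 102. The plan is two-tailed.
- 30% of 133 mL with the treated-arm SD of 96 in both arms gives 91. Nothing in the document supports that SD for placebo.

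**5. A caesarean-like scenario (assumption: 800–1200 mL already lost at inclusion, caesarean-trial SD unchanged).** Control additional loss is 2089 − 800 = 1289 mL down to 2089 − 1200 = 889 mL. For 30% at 103 per group, power is 23–46% on the raw scale (SD 1556 or the pooled 1495). On the log scale (SD 1556) it is 58–77%, and 81% in the most favourable case with all 114 evaluable.

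**The case against.** The strongest reply is that matching a number does not identify its inputs. The 56% calculation reproduces 103, but so does 30% of the caesarean trial's total bleeding with a Mann-Whitney adjustment. That second route agrees with the abstract's 30%, the caesarean setting and the planned non-parametric fallback. The words "considering a maximal 50% reduction as previously observed after higher dose administration" could also be read as a ceiling, with a lower low-dose assumption lost when the protocol was condensed into an article. This stands: a reader might infer that the low-dose arm was powered on the full high-dose effect, but the document never says so and it should not be asserted. If total bleeding was the basis, the number was computed on a variable other than the primary endpoint, and it still does not fit the 50% in the Methods.

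A second reply is that the SDs come from moderate haemorrhage after vaginal delivery, while this trial enrols caesareans with at least 800 mL lost, allows a log transformation and adjusts for baseline loss and centre. This also stands in part, and it is why the power figures must be given as conditional. Covariate adjustment alone would bring the raw-scale 30% comparison to 80% at 103 per group only if baseline loss correlated about 0.84 (SDs 252/96) to 0.91 (SD 252) with the outcome; the document claims no such value.

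Third, no sentence states 80% power for 30%. The abstract gives 30% without a power figure, and the Methods give 80% beside 50%. A reader may join the two, but the document does not.

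**Conclusion.** Wrong as written. The contradiction between 30% and 50% is on the page and needs no assumption. On the only T0–T360 data quoted, with the stated two-tailed 5% level and the two arms' own SDs, 103 per group matches the full 56% difference and neither stated effect.

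How far power falls short depends on inputs that the section leaves open. For a 30% reduction at 103 per group it is about 20–32% on the quoted T0–T360 figures, about 54% on a lognormal scale with the same mean and SD, and roughly 23–46% (raw) or 58–81% (log, the top value needing all 114) in the caesarean-like scenario. Most of these lie below 80%, but an unconditional statement that the trial is underpowered for 30% would go further than the document allows.

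Two further differences might be read as errors and are not counted. Rounding to 114 rather than 115 depends on convention (103 × 1.10 = 113.3; 103/0.9 = 114.4) and is immaterial. The background's "reduction of the bleeding volume (173 mL vs 221 mL in the control group" for the vaginal-delivery trial carries no time window or type of summary, so it is not shown to conflict with 133 vs 58 mL.

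**What to change.** Keep 342 patients. In the abstract and in the Sample size calculation section, state identically:
- one planning effect for placebo versus low dose on additional loss T0–T360;
- the control mean, the SDs, the test and the scale actually used to obtain 103.

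Then give the power that 103 evaluable patients per group provide for 30% and for 50%, as a range conditional on those inputs. Remove the abstract's statement that 342 was calculated for 30% unless the stated inputs support it. The sponsor should report the basis it really used; 56% should not be written in merely because it reproduces the number.

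The cost is a text correction in two places, with no additional patients. The downside is that the stated power will probably look less favourable.
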